#### Secondary outcomes

Our approach toward the secondary outcome analysis would be mainly exploratory and report the summary outcomes of the secondary outcome measures. We will check the distributions of the data whether following normal or not. For any continuous secondary outcomes (e.g. length of hospital stay, severity and duration of symptoms) we will report the mean and standard deviation, along with the outcome of statistical tests by groups (e.g. *t*-test). The categorical outcomes will be reported using percentages and chi-square tests. In all cases, a summary of the missing data will be reported. We will also report the safety data using summary statistics by the patients and the events for each of the trial arm groups.

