#### Secondary objectives

To determine:Whether carrageenan nasal and throat spray reduces the severity and/or duration of COVID-19 infection.Whether carrageenan nasal and throat spray reduces the risk of infection with other respiratory virusesThe usability of carrageenan nasal and throat spray for long-term prophylaxis against respiratory virusesThe effect of using the spray on quality-adjusted life years and cost-effectivenessWhether carrageenan nasal and throat spray reduces subsequent familial or household infection with COVID-19Whether any investigations or questionnaire findings in this trial offer a predictive value for acquiring COVID-19 infection or determining the severity and/or duration of resultant infectionAny associations between symptom severity and/or duration and prognosis with COVID-19

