### Randomisation

Following consent, baseline data will be collected, and the participants will be issued a randomisation ID which will assign them to either placebo or verum spray. This will be documented on the enrolment log. The randomised spray bottles will be stored at Swansea University, UK, for assignment to subject participants.

Randomisation sequence will be created using R 3.6.3 (R Core Team 2020) based on the pseudorandom number generation algorithm “Mersenne-Twister” using a 10-digit seed for reproduction. Participants will be assigned to the respective treatment with a 1:1 allocation and fixed block size by a statistician with no clinical involvement in the trial.

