#### Secondary outcomes

Severity and duration of symptoms (time taken for all symptoms to resolve, length of hospital and intensive care stay, mortality rate)Acquisition of non-COVID-19 respiratory viral infections, e.g. common cold or flu symptoms in non-COVID-19 positive participantsUsability and acceptability data of nasal and throat spray as prophylaxisEffect on quality-adjusted life years and cost-effectivenessSubsequent familial/household COVID-19 infectionBaseline haematological or questionnaire findings as predictors for acquiring COVID-19 infection or determining severity and/or duration of resultant infectionassociations between symptom severity and/or duration and prognosis with COVID-19

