### Sample size and rationale for non-inferiority

We calculated the sample size based on the primary outcome measures (having COVID-19) and the respective assumed effect size in relation to the intervention (receiving iota-carrageenan spray) and the placebo nasal spray (0.5% saline). The magnitude of any effect of the nasal and throat spray on COVID-19 symptoms is unknown. However, 20.2% of healthcare professionals reported at least one symptom associated with SARS-CoV2 infection during the first wave of the pandemic, with a twelvefold increase in the risk of a positive test compared to the general population [4]. It has been recognised that key workers have been disproportionately affected by COVID-19 infections and the overall seroprevalence of SARS-CoV-2 antibodies has been found to be 24.4% in healthcare professionals [52, 53]. .Assuming an expected difference of 12.5% (i.e., 25% and 12.5% in the intervention and control group respectively), a sample of 304 participants (i.e. 152 in each arm) will provide 80% statistical power using a two-sided significance level of 5%. Assuming a lost to follow-up of 20%, a total of 380 participants (190 in each arm) will be needed.

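### Non-COVID respiratory illness is counted only in participants who stay COVID-negative, a group formed after randomisation, and the example method for symptom duration ignores censoring

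*Protocol article*

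**What the plan says.** Under Outcomes, the secondary outcome on other respiratory viral infections is illustrated as "common cold or flu symptoms in non-COVID-19 positive" participants. The same list includes severity and duration of symptoms (time until every symptom has gone, hospital and intensive care stay, mortality) and names no population for them. The Secondary objectives ask whether "carrageenan nasal and throat spray reduces the severity and/or duration of COVID-19" infection.

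The opening paragraph of Statistical analysis commits to intention-to-treat and makes no exception for secondary outcomes. Its Secondary outcomes paragraph calls the approach mainly exploratory, plans a check of distributions, and continues: "For any continuous secondary outcomes (e.g. length of hospital stay, severity and duration of symptoms) we will report the mean and standard deviation". Tests by group follow, with the t-test as the example. The article names no alternative test. It does not say how unresolved symptoms, deaths or uninfected participants enter a duration.

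**The concern.** An outcome assessed only in COVID-negative participants compares groups that randomisation did not create. If the spray works, the spray arm keeps people who would have been infected on placebo. If those people also meet more respiratory viruses in general, the spray arm will show more colds and flu with no effect of the spray on them. This is plausible here, because Revision to trial design widens recruitment to key workers and others who must mix outside their household.

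For duration, a mean and a t-test treat a symptom spell cut off by the end of the tracker as if it had ended then. They also give no sensible value to a participant who dies unresolved. Severity is half of the research question, so the comparison behind it should be one that randomisation protects.

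**Working it through.** **Inputs from the article.** The sample size section gives the rates: "Assuming an expected difference of 12.5% (i.e., 25% and 12.5% in the intervention and control group respectively". Its target is 152 evaluable people per arm (304 in all) for 80% power at two-sided 5%, raised to 380 for 20% loss. As printed, the higher rate falls to the intervention arm. I read the rates as placebo 25% and spray 12.5%; the sample size does not depend on the order.

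**The plan's own figure.** Two proportions, pooled variance, two-sided 5%, no continuity correction: 152 per arm, with power 80.03% at 152. 304/(1 - 0.20) = 380. Both reproduce.

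**Group sizes on those rates.**
- COVID-negative: placebo 152 × 0.75 = 114; spray 152 × 0.875 = 133.
- Infected: placebo 152 × 0.25 = 38; spray 152 × 0.125 = 19.

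**Non-COVID illness, by hand.** Assume no effect on other viruses, a 30% risk in general, and a 50% risk in the 19 people whom the spray spared COVID-19. Placebo: 30.0%. Spray: (114 × 0.30 + 19 × 0.50)/133 = 43.7/133 = 32.9%.

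**Non-COVID illness, with shared exposure.** Each person has exposure multiplier F = exp(s·Z), with Z standard normal. The risk of each infection is 1 - exp(-λF). λ is set so that the average risk is 25% (COVID-19, placebo), 12.5% (COVID-19, spray) and 30% (other viruses, both arms). The plan's restriction gives E[exp(-λF)(1 - exp(-λ'F))]/E[exp(-λF)], where λ is the arm's COVID-19 rate and λ' the rate for other viruses.

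| Log-hazard SD s (assumed) | Spray | Placebo | Difference, points |
|---|---|---|---|
| 0 | 30.0% | 30.0% | 0 |
| 0.5 | 29.2% | 28.3% | 0.9 |
| 1 | 27.1% | 24.3% | 2.8 |
| 1.5 | 24.9% | 20.4% | 4.5 |

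Counted in everyone, both arms show 30% in every row. The standard error of the restricted difference at a rate near 25% is √(0.25 × 0.75 × (1/133 + 1/114)) = 5.5 points. The bias is therefore at most about 0.8 standard errors here.

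**Duration, if infected participants only were compared.** The article gives no duration distribution, so this is illustrative. Duration is exp(2 + 0.8z) days, and the spray changes no infected person's duration. It prevents a would-be infection with probability 1/(1 + exp(slope·z)), which averages 50%. A positive slope means that mild cases are prevented more often.

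| Slope (assumed) | Spray minus placebo, days | Pooled t-test declares spray worse |
|---|---|---|
| -0.75 | -2.6 | 0.2% or less |
| 0 | 0 | about 3% |
| 0.5 | about +2 | about 11% |
| 1.5 | +4.1 | about 33% |

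The nominal rate in the last column is 2.5%. At slope 1.5 a Welch test reduces it to about 25%. A second model, with correlation -0.5 to 0.7 between susceptibility and log duration, gives -1.0 to +4.3 days and 0.4% to 20% false harm. The subset is also small: at 80% power the detectable effect is (1.960 + 0.842) × √(1/38 + 1/19) = 0.79 SD.

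**Censoring.** In that second model (median 10 days at average susceptibility, log-SD 0.7, onset uniform over 70 days), 11% to 33% of infected participants are unresolved at day 70.

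**Zeros.** If uninfected participants enter as zero, t-test type I error at 152 per arm is 5.1%, 4.8% and 4.7% with 25%, 12.5% and 5% non-zero values. With 2% and 1% non-zero it falls to 2.6% and 0.9%. Zeros cost power; they do not create false positives.

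**The case against.** The restriction to COVID-negative participants appears inside an example, and the t-test is likewise an example, offered after a distribution check in analyses called mainly exploratory. Choice of alternative test, handling of censoring and exact analysis sets are ordinary content for an analysis plan or full protocol not shown here. This argument stands for severity and duration. A reader might infer that the plan compares them in infected participants only. The objective points that way, but no section says so, and the stated principle is intention-to-treat. Nor can infected-only selection and zeros from uninfected participants both apply to symptom duration; hospital stay alone could be mostly zero among the infected.

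The bias figures rest on assumed selection. The non-COVID bias is smaller than one standard error. Scoring uninfected participants as zero also answers a different question: in the duration simulation that rank test rejects in 72% to 84% of trials, against 80% to 81% for the primary chi-square test, although no infected person's duration changes. It largely re-tests infection.

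What does not fall is the following. The COVID-negative restriction is the only operational definition given for that outcome, and it contradicts the article's own analysis principle. A distribution check cures neither selection nor censoring. Ethics and auditing also commits to submitting each secondary endpoint for publication, so the exploratory label does not remove the need for an interpretable comparison.

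**Conclusion.** The concern holds in two limited parts. First, the non-COVID outcome is defined in a group selected by the primary outcome, in conflict with intention-to-treat. With no effect on other viruses, the spray arm looks worse by 0, about 1, about 3 or 4.5 points at assumed exposure SDs of 0, 0.5, 1 and 1.5. Second, mean, SD and a t-test are a poor example for time to resolution, which is censored at study end and by death.

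For severity and duration, the accurate statement is that the comparison population is open. A reader might infer that the spray will look harmful or useless. The documents do not support that. The bias arises only if infected participants alone are compared; it is zero without selection on severity, and it can favour the spray. Its range of about -2.6 to +4.1 days rests on assumed slopes of -0.75 to 1.5. The primary outcome is unaffected.

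**What to change.** 1. **Non-COVID illness.** Count symptomatic episodes not attributed to COVID-19 in all analysed randomised participants, whatever their COVID status. Add a sensitivity analysis for participants positive by serology only, whose episodes cannot be attributed with certainty.
2. **Severity and duration.** Make the between-arm comparison in all analysed randomised participants by a rank-based method. Use either a ranked severity scale running from uninfected to death, or COVID-symptom days with 0 if uninfected. State that this measures total burden and so includes the infection-prevention effect.
3. **Time to resolution among the infected.** Report by Kaplan-Meier, censored at the end of the tracker and with death never counted as resolution, as descriptive only. State the tracker's end: the Abstract gives 10 weeks, while Treatment arms/intervention describes an 8-week trial with the daily tracker.
4. **Wording.** Remove the t-test as the example for these outcomes.

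The daily tracker, PCR and serology already supply the data. The cost is minor analysis work and a burden estimand that overlaps with the primary outcome. It does not isolate an effect on severity once infected; the infected-only description bears on that question but is not protected by randomisation.

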#### Quality of life data

Quality of life data will be collected using the EuroQol 5-dimension, 3-level (EQ-5D-3L) patient-reported outcome measures (PROM) [50]. This widely used, patient-completed PROM gathers generic data on health-related quality of life at specific time points when completed. The EQ-5D-3L is used on the advice of the NICE 2019 position statement, recommending its use over the new EQ-5D-5L [51]. Questionnaires will be completed at enrolment, week 4 and week 10 (study end).

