#### Baseline assessment

Participant demographics including date of birth, gender and ethnicity will be recorded. Medical history will be recorded including current medical conditions, regular medications, and any allergies. Participants will be asked to complete a quality-of-life questionnaire: EQ-5D-3L, this will also allow for a later cost-effectiveness analysis as well as undergo the baseline blood tests outlined above. Randomisation and training in spray application will take place after baseline assessments and questionnaires have been completed, on the same day.

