#### Primary outcome

The primary outcome measure is a binary variable whether COVID-19 infection has been confirmed by PCR swab or not. We will perform a summary analysis reporting the outcome of the categories of two trial arms with respect to the primary outcome measure. The odds ratio and related statistical significance of the chi-square test will be reported. Following on, an adjusted analysis will be done adopting a logistic regression model. The adjustment would be done using the baseline covariates like demographics, co-morbidities (especially history of COVID-19), current medications along with baseline QoLs. The selections of the covariates would be done based on literature reviews along with discussing with the clinical co-applicants involved in this trial. This will also depend on the missing of the covariates and the selection procedure in the statistical modelling.

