### Economic evaluation

An economic evaluation will be undertaken at day 70 post randomisation. The proposed secondary endpoints and methods for economic evaluation follow the guidance set out by NICE [54]. The primary economic analysis will be a cost-utility analysis expressed in terms of quality-adjusted life years (QALYs). Cost data based on the cost of a course of active ingredient spray will be obtained from the supplying company (Marinomed Biotech AG). A comparator cost analysis will be performed for the cost associated with developing COVID-19. A number of models will be developed, expressing the predicted cost of falling ill with COVID-19 but remaining at home, the cost associated with a short hospital stay and finally that associated with an admission to critical care. Treatment costs will include the cost of each scenario including healthcare professionals, equipment and infrastructure costs. Incremental cost-effectiveness ratios, incremental net monetary benefit and incremental net health benefit statistics will be calculated. A QALY in the range of £20,000–£30,000 will be considered acceptable in line with NICE guidance [54].

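### As written, QALYs fall under the general unadjusted rule for continuous secondary outcomes; adjusting for the baseline EQ-5D-3L already collected would make the QALY difference more precise at almost no cost

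*Protocol article*

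**What the plan says.** - **Status of the outcome.** The secondary outcomes listed under Outcomes include the effect on QALYs and cost-effectiveness.
- **General rule.** Under Statistical analysis, Secondary outcomes, the scope is "For any continuous secondary outcomes (e.g. length of hospital stay, severity and duration of symptoms" and the method is "we will report the mean and standard deviation, along with the outcome of statistical tests by groups". The t-test is given as an example and no covariate is named. The same section says "Our approach toward the secondary outcome analysis would be mainly exploratory".
- **Economic analysis.** The Economic evaluation section says "The primary economic analysis will be a cost-utility analysis expressed in terms of quality-adjusted life years (QALYs" and "The proposed secondary endpoints and methods for economic evaluation follow the guidance set out by NICE". It sets the evaluation at day 70 and plans ICERs, incremental net monetary benefit and incremental net health benefit. It does not say how a QALY is built from EQ-5D-3L, and it does not mention baseline utility.
- **Data collected.** Quality of life data: "Questionnaires will be completed at enrolment, week 4 and week 10 (study end". Baseline assessment places the enrolment EQ-5D-3L before randomisation and says of it that "this will also allow for a later cost-effectiveness analysis".
- **Where baseline quality of life is used.** Under Statistical analysis, Primary outcome, the covariates for the logistic model of infection include "current medications along with baseline QoLs". No other model names it.

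**The concern.** Baseline utility is likely to be the best single predictor of a participant's 10-week QALY, and under the usual construction it is also a component of it. The plan intends to adjust for baseline quality of life when the outcome is infection. It does not say so for the outcome where the adjustment would help most.

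The QALY difference is the denominator of the ICER and enters both net-benefit statistics. Over 70 days, in people of working or studying age whose illnesses are mostly short, it is likely to be small relative to its standard error. Variation between arms in starting utility then makes up a large part of the noise in the cost-effectiveness result, and data already in hand could remove it.

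**Working it through.** **The plan's own figure.** The only design calculation is for infection. With rates of 25% and 12.5%, two-sided 5% and 80% power, the pooled-variance formula gives

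n per arm = [1.96·√(2 × 0.1875 × 0.8125) + 0.8416·√(0.25 × 0.75 + 0.125 × 0.875)]² / 0.125² = 151.9, so 152 per arm and 304 in total.

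Allowing for 20% loss, 304 / 0.8 = 380. The stated figures reproduce. They do not bear on QALYs, except that 152 per arm is used below.

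**Inputs from the article.** EQ-5D-3L at weeks 0, 4 and 10; horizon of 70 days (10 weeks); 1:1 allocation; 152 evaluable per arm; £20,000 to £30,000 per QALY.

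**Inputs assumed, because the article gives none.**
- QALY as the trapezoidal area under the utility curve.
- Equal utility SDs at the three visits.
- A common correlation ρ between visits, from 0 to 0.7.
- For the money figures only, a utility SD of 0.15.

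**Step 1: weights.** The intervals are 4 and 6 weeks. Baseline gets 4/2 = 2 weeks, week 4 gets (4 + 6)/2 = 5, and week 10 gets 6/2 = 3. As shares of 10 weeks these are 0.2, 0.5 and 0.3.

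**Step 2: variance explained by baseline.** In units of the utility variance, for mean utility over 10 weeks:
- Variance = 0.2² + 0.5² + 0.3² + (1 − 0.38)ρ = 0.38 + 0.62ρ
- Covariance with baseline = 0.2 + 0.8ρ
- R² = (0.2 + 0.8ρ)² / (0.38 + 0.62ρ)
- Adjusted SE / unadjusted SE = √(1 − R²), a large-sample figure
- Equivalent multiplier of the unadjusted sample = 1/(1 − R²)

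| ρ | Variance | Covariance | R² | SE ratio | SE cut | Equivalent n |
|---|---|---|---|---|---|---|
| 0 | 0.380 | 0.20 | 0.105 | 0.946 | 5% | ×1.12 |
| 0.3 | 0.566 | 0.44 | 0.342 | 0.811 | 19% | ×1.52 |
| 0.5 | 0.690 | 0.60 | 0.522 | 0.692 | 31% | ×2.09 |
| 0.7 | 0.814 | 0.76 | 0.710 | 0.539 | 46% | ×3.44 |

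There is a gain even at ρ = 0, because baseline is itself part of the assumed QALY.

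**Step 3: scale in QALYs and pounds.** The unadjusted SE is 0.15 × √(0.38 + 0.62ρ) × (10/52) × √(2/152). The half-width is 1.96 × £20,000 × SE. It covers only the QALY part of net monetary benefit and leaves out cost variation.

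| ρ | SE unadjusted | SE adjusted | 95% half-width unadjusted | 95% half-width adjusted |
|---|---|---|---|---|
| 0.3 | 0.00249 | 0.00202 | £98 | £79 |
| 0.5 | 0.00275 | 0.00190 | £108 | £75 |
| 0.7 | 0.00299 | 0.00161 | £117 | £63 |

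At £30,000 per QALY, multiply the half-widths by 1.5.

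**Step 4: chance imbalance.** One standard error of the baseline difference is 0.15 × √(2/152) = 0.0172. It passes into the unadjusted QALY difference at (2 + 8ρ)/52 per unit of utility.
- ρ = 0.3: 0.0172 × 0.0846 = 0.0015 QALY, or £29 per person at £20,000.
- ρ = 0.7: 0.0172 × 0.1462 = 0.0025 QALY, or £50 per person at £20,000.

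These shifts are 58% and 84% of the unadjusted SE. They are already counted within that SE. Adjustment removes them.

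**The case against.** The strongest reply is that the general rule was never meant for QALYs. Its named examples are length of stay and symptom severity and duration, none of which has a pre-randomisation value. The t-test is only an example, and the section describes itself as mainly exploratory. QALYs have their own later section, which refers to NICE guidance and plans ICERs and net benefit without mentioning a t-test. A specific section normally governs over a general one. The article is also a condensed account, so the regression details may sit in the full protocol, the SAP or a health-economic plan, none of which is shown.

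Much of this stands. A reader might infer that the trial has committed itself to an unadjusted t-test as the basis of its cost-utility result. The documents do not support that: the Economic evaluation section is silent on adjustment, and the content of the NICE guidance is not in the article. A reader might also infer that chance baseline imbalance biases the cost-effectiveness result. It does not. Under 1:1 randomisation the unadjusted difference is unbiased, and its standard error already reflects such imbalance.

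The size of the gain is uncertain too. It depends on the QALY construction, the equal SDs and the correlation. If most recruits start near the top of the utility scale, baseline varies little or predicts weakly, and the gain moves towards or below the lower end of the range.

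The reply does not remove the point. The rule is written for all continuous secondary outcomes, QALYs are listed among the secondary outcomes, and nothing in the article takes them out of its scope. This is a stated method that reaches an outcome for which a better one is available, and not only a missing detail.

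**Conclusion.** The point holds as a near-free improvement of low to moderate priority. As written, QALYs come under an unadjusted comparison of group means, and the economic section does not override it. With an area-under-the-curve QALY, equal SDs and a common correlation of 0 to 0.7 (all assumed), adjusting for baseline utility cuts the standard error of the QALY difference by about 5% to 46%. No correlation in that range favours the unadjusted comparison.

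The loss is one of precision, not validity. Priority is limited because the outcome is secondary and the analysis mainly exploratory, and because the planned economic model may already include the adjustment in a document that is not shown.

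**What to change.** In Statistical analysis, Secondary outcomes, and in Economic evaluation:
- State that the QALY difference is estimated by linear regression of each participant's 10-week QALY on arm and baseline EQ-5D-3L utility, with robust or bootstrap standard errors because utilities are skewed.
- State that this adjusted difference is the one used in the ICER, incremental net monetary benefit and incremental net health benefit.
- Keep the raw means and SDs by arm as description.

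If the adjustment is already specified elsewhere, it is enough to say that the general rule for continuous secondary outcomes does not govern QALYs and to point to where the method is set.

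The cost is a sentence or two of wording, one model term and one degree of freedom. No new data, visits or participants are needed, because EQ-5D-3L is already collected before randomisation.
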